#### Secondary outcome measures

Secondary *outcome measures* will consist of physiological parameters, any adverse reactions observed, satisfaction from caregivers, acceptance of patients, and additional use of analgesics during the intervention. The duration of the intervention will also be included in the secondary outcomes.

### Sample size estimation

After obtaining the ethical approval of our study protocol, a preliminary experiment with a sample size of 30 was conducted in Nursing Home, Yinchuan, in January 2020. The results of the pilot study indicated that the FPS-R score of the control group and the intervention group was 5.97 ± 1.81 and 4.79 ± 1.96, respectively. We have consulted a statistician from the School of Medical Statistics and Epidemiology at Ningxia Medical University, who finished the randomization list of the recruits. With a type 1 error rate of 0.05 (*α* = 0.05, two-tail) and a 90% power (*β* = 0.10), the sample size of the study scheme was calculated by the statistical expert, which was 86 patients in each group. According to our study design and considering the particularity of this research subject (they are less likely to complete the entire experiment), we assume a 20% drop-out rate. The total sample size of 206 cases (per group was 103 cases) is required to reduce the underpower of the study.

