### Outcome measurement

#### Primary outcome measure

The level of pain relief at T1 and T2 will be considered as the primary outcome. It is accurately recorded by a researcher in charge of recording on the basis of the FPS-R.

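### The planning figures under Sample size estimation disagree: the printed pilot inputs give about 54 patients per arm, not 86, and the origin of the pilot means needs stating

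*Protocol article*

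**What the plan says.** Under Sample size estimation the Protocol article reports that "a preliminary experiment with a sample size of 30 was conducted in Nursing Home, Yinchuan, in January 2020". It gives the result as "the FPS-R score of the control group and the intervention group was 5.97 ± 1.81 and 4.79 ± 1.96, respectively". It does not say how many of the 30 were in each arm, at which assessment the scores were taken, or whether the means are raw.

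The calculation follows directly: "With a type 1 error rate of 0.05", two-tailed, with 90% power, giving a size "which was 86 patients in each group". This is raised to 103 per group, 206 in total, for an assumed 20% drop-out. No other difference or SD is given.

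Under Primary outcome measure the article says: "The level of pain relief at T1 and T2 will be considered as the primary outcome". FPS-R is scheduled at T0, T1 and T2 (Table 1).

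**The concern.** The pilot means and SDs are the only stated basis for 86 per arm and 90% power. A reader should be able to put them into the standard two-means formula and obtain the stated size. That fails by a wide margin, so the figures used were not those printed, or the calculation was not the one described.

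A second check concerns the means themselves. When scores are whole numbers and arms are small, only certain two-decimal means can occur. A control mean of 5.97 is hard to obtain from about 15 patients. If the printed values are not FPS-R scores at one time point, their SDs may not describe the outcome at T1 or at T2, and the stated 90% would not be the power for the declared primary outcome. What is at stake is whether the stated size and power can be relied on, not how many patients to enrol.

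**Working it through.** **Inputs.** From Sample size estimation: means 5.97 and 4.79, SDs 1.81 and 1.96, pilot n = 30, two-sided alpha 0.05, power 90%, stated n = 86 per arm. Assumed, because the article does not say: whole-number FPS-R ratings, and (step 4 only) the within-patient correlation between T1 and T2.

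**1. Trying to reproduce 86.** Per arm, n = (1.960 + 1.2816)² × (s₁² + s₂²) / Δ².

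- Δ = 5.97 − 4.79 = 1.18, so Δ² = 1.3924
- s₁² + s₂² = 1.81² + 1.96² = 7.1177
- n = 10.507 × 7.1177 / 1.3924 = 53.7, so 54 per arm

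Other readings do not reach 86 either:

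| Variant | n per arm |
|---|---|
| t-test instead of normal approximation | 55 |
| SD 1.81 in both arms | 50 |
| SD 1.96 in both arms | 58 |
| One-sided | 44 |
| 95% power | 67 |
| Alpha 0.01 | 77 |
| Wilcoxon efficiency correction | 57 to 63 |

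With the other inputs held, 86 at 90% power needs a common SD of 2.39, or a difference of 0.93.

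**2. Power at 86 on the printed inputs.** Φ(1.18 / √(7.1177/86) − 1.960) = Φ(4.102 − 1.960) = Φ(2.142) = 98.4%, not 90%.

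**3. Can the means arise from 30 patients?** For whole-number scores at one time point, some integer total divided by n must round to the printed mean.

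- For n up to 30, 5.97 occurs only at n = 29 and 30.
- For n up to 30, 4.79 occurs only at n = 14, 19, 24, 28 and 29.
- No pair adds to 30 or fewer, so missing scores do not help.
- With 15 per arm the nearest means are 89/15 = 5.93 or 90/15 = 6.00, and 71/15 = 4.73 or 72/15 = 4.80.
- Truncating the decimals, or scores in 2-point steps, gives no split of 30 either.

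If 30 is per arm, 179/30 = 5.97 fits, but 143/30 = 4.77 and 144/30 = 4.80 miss 4.79. With 28 or 29 scores the mean 4.79 is possible (134/28, 139/29), but SD 1.96 is not. The sum of squares would have to be 745 with total 134, or 774 with total 139. A sum of squared integers has the same parity as the sum, and neither pair does.

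Other derivations do fit the means:

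- Per-patient averages of two assessments fit at 16/14 and 18/12 with all 30 analysed, and at others such as 15/14 with some missing.
- Averages of three assessments fit at 11/19 and 22/8, and at 30/30 if 30 is per arm (537/90 = 5.97, 431/90 = 4.79).
- One-decimal scores fit at 15/15, for example 89.5/15 and 71.8/15.
- Adjusted means have no such constraint.

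In 2-point steps, neither kind of average fits any split of 30.

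**4. If the inputs are T1/T2 averages.** An average of two scores with equal SDs and correlation ρ has variance (1 + ρ)/2 times that of a single score. A single-time analysis with the same difference therefore needs 53.7 × 2/(1 + ρ) per arm.

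| ρ (assumed) | n per arm for 90% | Power at 86 |
|---|---|---|
| 0.25 | 85.9 | 90% |
| 0.5 | 71.6 | 94% |
| 0.8 | 59.7 | 97% |

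**The case against.** The strongest reply is that the check on the means rests on a premise the article never states. The eligibility criteria give only an entry threshold of 4, and Measurement and Primary outcome measure name the scale without its scoring steps. Nor does the article call the pilot values raw means at a single time point. Three assessments are scheduled, the abbreviation list includes ANCOVA, and the pilot design is not shown, so averaged or adjusted means cannot be excluded. A journal article may also leave pilot details to the full protocol.

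All of this stands. A reader might infer from step 3 that the pilot data are erroneous. The documents do not support that, because the check cannot separate wrong figures from briefly described ones. It raises a query only.

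The reply does not reach steps 1 and 2. The mismatch between 54 and 86 needs no assumption about scoring, and it lies in what the article prints, not in what it leaves out.

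A second reply concerns harm: every scenario worked above needs 86 per arm or fewer. That also stands.

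**Conclusion.** The stated basis for 86 per arm is wrong as written. The printed inputs give about 54 per arm at 90% power, or about 98% power at 86. This rests only on the article's own numbers and the usual two-means formula.

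The query about the pilot means is conditional. If FPS-R ratings are whole numbers, 5.97 and 4.79 cannot both be raw single-time-point means from any split of 30 patients. Averages over assessments, adjusted means, finer scoring or a different pilot n could explain them.

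A reader might also infer that the trial is underpowered. That is not shown. Under assumed correlations of 0.25 to 0.8, power at 86 per arm is about 90% to 97%. The correlation would have to be below about 0.25 for 86 to fall short, since 2 × 53.7/86 − 1 = 0.249, and nothing in the article suggests that it is. The defect is in how the size is justified. It should be corrected, but it gives no reason to change the number enrolled.

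**What to change.** Check the pilot data, then revise Sample size estimation to state:

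- the number of pilot patients in each arm, and whether 30 is the total or per arm;
- the assessment at which the scores were taken, and whether the means and SDs are raw, averaged over assessments or adjusted;
- the difference and SD actually used to reach 86;
- the required size, or the power at 86 per arm, for the declared primary outcome at T1 and T2.

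The cost is re-reading a small data set and rewriting one paragraph. Restating the power is enough, and enrolment need not change.

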## Methods

### Study design

This study is a multi-center and single-blind, randomized, sham-controlled clinical trial. It aims to compare and analyze the one-time analgesic effect between the intervention group and the sham-controlled group (Fig. 1, Table 1) for acute pain in patients with dementia. This trial, superiority framework, was designed on the basis of SPIRIT guidelines and the Consolidated Standards of Reporting Trials (CONSORT) statement [18, 19]. The Ningxia Medical University Ethics Committee has given its official approval for the study protocol, which has been registered at the Chinese Clinical Trial Registry (No.: ChiCTR2100047932). Each patient will be given a detailed explanation by the researcher including the purpose, benefits, and potential risks of the study. Moreover, they can withdraw from the study at any time, and this will not affect medical services other than the research. Subsequently, the qualified recruits who signed informed consent entering the study will receive APP or shamed APP treatment by an investigator, a master candidate in nursing science with APP professional training. It is needed to make important protocol modifications to reduce underpower of the study protocol and increase patient safety. We will communicate with the Data Management and Safety Monitoring Committee (DMSMC), all participants, and the Ethics Committee.

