### Patients

All 206 patients who met the inclusion and exclusion criteria are being recruited from the three nursing homes. Recruitment is expected to take place from December 2020 to December 2021. The recruits with informed consent before entering research will be randomly allocated to an intervention or a sham-controlled group in a 1:1 ratio. Furthermore, it is feasible to have enough patients to meet the target sample size in three nursing homes. The inclusion criteria include the following: (1) aged 60 or above with speaking Chinese, (2) dementia was diagnosed by the Diagnostic and Statistical Manual of Mental Disorders (DMS-V) criteria [20], (3) diagnosis of mild dementia based on the Montreal Cognitive Assessment (MoCA) [21], (4) acute pain and a score of pain ≥ 4 based on the Face Pain Scale Revised (FPS-R), (5) able to be monitored by pulse oximetry, (6) understanding the meaning of the FPS-R, and (7) volunteering to participate in the study and signing the informed consent (caregivers, patients, and/or family members). The exclusion criteria are as follows: (1) moderate or severe dementia, (2) medical contraindication for ear acupressure (inflammation, ulcers, frostbite in the ear), (3) history of allergy to adhesive tape and alcohol, (4) critically ill patients who have no response to the effectiveness and safety of new treatments (serious heart, brain, liver, kidney, or hematopoietic system diseases), and (5) patients who received drugs for pain management and other interventions. Once the subjects were enrolled, written informed consent from all patients and their caregivers was obtained by the researchers.

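### The 86 per group does not follow from the pilot figures, alpha and power printed beside it (they give 54 or 55), so the effect behind 86 is not stated

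*Protocol article*

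**What the plan says.** The point lies in the Sample size estimation section of the protocol article. It reports a pilot of 30 patients ("a preliminary experiment with a sample size of 30 was conducted") and its result: "the FPS-R score of the control group and the intervention group was 5.97 ± 1.81 and 4.79 ± 1.96, respectively". It then sets a two-sided type 1 error of 0.05 and 90% power and concludes that "the sample size of the study scheme was calculated by the statistical expert, which was 86 patients in each group". For loss to follow-up, "we assume a 20% drop-out rate", which takes the total to 206, or 103 per group.

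Two other sections complete the inputs. Under Patients, participants are "randomly allocated to an intervention or a sham-controlled group in a 1:1 ratio". Under Study design, the trial has a superiority framework. The article names no other difference, SD, significance level, design effect or rank-test correction for the calculation.

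**The concern.** The paragraph reads as a complete derivation: two means, two SDs, alpha, power, then a number per group. A reader who repeats it with the standard two-sample formula gets a number about a third smaller. Either 86 came from assumptions that are not printed, or the calculation is wrong.

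At stake is what the trial was built to detect. If the pilot values were the planning inputs, the 90% power is not the power at 86, and about 31 more evaluable patients per group (86 − 55) are sought than the stated reasoning requires. If something else was used, the pilot figures are not the justification they appear to be. Neither a reader nor the ethics committee can tell which.

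**Working it through.** **Inputs.** All are from Sample size estimation, except the 1:1 allocation (Patients): control 5.97, SD 1.81; intervention 4.79, SD 1.96; two-sided alpha 0.05; power 90%; stated result 86 per group; drop-out 20%; final 103 per group.

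**Step 1: the standardised difference.**
- Difference = 5.97 − 4.79 = 1.18.
- Pooled SD = √[(1.81² + 1.96²)/2] = √3.559 = 1.886.
- d = 1.18/1.886 = 0.6255.

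**Step 2: try to reproduce 86.**
- Normal approximation: n = 2(1.960 + 1.282)²/d² = 21.01/0.3912 = 53.7, so 54 per group.
- Exact two-sample t-test (noncentral t): 54.7, so 55 per group.
- 86 is not reproduced; 86/55 = 1.56, so the printed figure is 56% higher.

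**Step 3: variants that keep the difference at 1.18 and power at 90%** (t-test, per group).

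| Variant | n |
|---|---|
| SD 1.81 | 51 |
| SD 1.96 | 59 |
| Rank test, efficiency 0.955 | 58 |
| Rank test, worst-case efficiency 0.864 | 64 |
| One-sided alpha 0.05 | 45 |
| Alpha 0.025, for two time points | 65 |
| SD 1.96, alpha 0.025 and efficiency 0.864 together | 81 |

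None reaches 86. Drop-out is not the explanation, because that allowance is added after 86: 86 × 1.2 = 103.2, which gives the 103.

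**Step 4: what 86 per group delivers** (t-test).
- Power for 1.18 at SD 1.886: 98.3%.
- Standardised difference detectable with 90% power: 0.497, or 0.497 × 1.886 = 0.94 points (normal approximation: 0.494, or 0.93 points).
- SD needed for 86 to be right at a difference of 1.18: 1.18/0.497 = 2.37, above both pilot SDs.

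**Step 5: after drop-out.** A 20% loss from 103 leaves 103 × 0.8 = 82.4, about 82 per group. If those lost add no information, power for 1.18 is 97.8%.

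**Step 6: which smaller effects give 86?**
- d = 0.50 needs 85.03 by t-test, so 86. By the normal approximation it needs 85.
- It is not the only route. A difference of 1.0 with SD 1.96 needs 81.7 by t-test, and 81.7/0.955 = 85.6, so also 86 with a rank-test correction.
- Power at d = 0.50 is 90.3% with 86 per group and 88.9% with 82.

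**The case against.** The strongest reply is that nothing harmful follows. The section never says that 1.18 was the planning difference; it reports the pilot and then says that a statistician calculated 86. A pilot of 30 is imprecise. If it was split 15/15, which is an assumption, the standard error is 1.886 × √(2/15) = 0.689 and the 95% interval is 1.18 ± 2.048 × 0.689, or −0.23 to 2.59. Planning for less than 1.18 would then be prudent. The article is also a condensed account, and a fuller document may hold the method.

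Much of this stands. It rules out two stronger readings:

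- A reader might infer that the article misstates the effect the trial is powered for. It does not support that, because it states no planning effect. What can be said is that the effect is not given and that the inputs printed in its place do not yield 86.
- A reader might infer that d = 0.50 was the real input. It fits, but the article never mentions it, and Step 6 shows another route to the same number.

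The reply does not remove the inconsistency. A condensed article may leave out a derivation, but this one prints inputs and a result that disagree.

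Two related points are secondary and add nothing to the arithmetic. The pilot scores are not tied to T1 or T2. They are also scores, whereas the primary outcome is worded as pain relief, although comparing post-treatment scores between randomised groups is a legitimate way to measure relief.

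**Conclusion.** The concern holds as an error in a stated figure. The only inputs given need 54 or 55 per group, not 86. This rests on a two-group comparison of means with equal allocation at the stated alpha and power, and the variants examined at a difference of 1.18 do not rescue 86.

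It is not a power shortfall for 1.18: power stays near 98% both at 86 per group and at about 82 completers. Whether the stated 90% is met for the effect actually planned cannot be judged until that effect is disclosed. Severity: should-fix.

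**What to change.** Keep N and correct the Sample size estimation paragraph. State the effect size, SD, test and time point actually used, so that a reader can reproduce 86. Then:

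- If the pilot values were the inputs, restate the required number as 55 per group and the power as about 98% at 86 (97.8% at about 82 completers).
- If d = 0.50 was used, say so, and give the power after 20% loss from 103 as about 89%, not 90%. It should not be declared merely because it fits.
- If something else was used, such as a smaller difference or a rank-test correction, state it with its value.

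In each case, say which time point the pilot scores refer to. The cost is the wording of one paragraph and a query to the statistician who did the calculation; recruitment is unaffected.

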### Management and safety monitoring

Prior to the study, research team members will receive a training program, which will cover the research design, procedure, evaluation of outcome measures, randomization, data collection, and data monitoring. For example, data recorders will be trained on how to collect and manage data to ensure the objectivity, quality, and safety of data as far as possible. Patients were anonymous throughout the trial. All subject’s personal information will also be stored in a separate envelope. It will then be saved in a Microsoft Access (Microsoft Office 2010, Redmond, WA, USA) database, which is password protected [23]. A separate code was generated by pre-randomization and kept by the project manager. It is a unique identifier that identifies anonymized data. With the consent of the project leader, only members of the research team have access to the collected information for a reasonable reason [24]. Another Microsoft Access database will be used to store all trial data. It can only be got by the data collectors, the investigator, and the DMSMC. It is necessary although the APP treatment was the least risky. It consisted of the project manager, principal researcher and physician of each sub-center, and experts from the Ethics Committee of Ningxia Medical University. They are primarily responsible for the quality control of clinical trials, including but not limited to the data collection and management and uniform training for investigators. Regular monitoring and auditing data will be also required. It should be also noted that the trained data collectors and investigators are fixed and that data quality control is carried out through double-entry bookkeeping by them [23, 24]. In addition, information on patients with withdrawal will not be included in the final analysis, and other researchers will investigate what led them to withdraw from the trial. According to previous studies, the side effects of this intervention have been reported rarely. Conducting an interim analysis or stopping rules will not be applied to the current study. All of the study subjects were elderly patients, so they will be closely monitored as part of the standard of care before, during, and after study participation.

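### The total of 206 protects the required 86 per group only up to about 16.5% drop-out, not the 20% the protocol assumes

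*Protocol article*

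**What the plan says.** All the figures are in the protocol article under Sample size estimation. The error rates are given as "With a type 1 error rate of 0.05" ("0.05, two-tail) and a 90% power"). The pilot result is reported as "the FPS-R score of the control group and the intervention group was 5.97 ± 1.81 and 4.79 ± 1.96, respectively". The calculated size is reported as "which was 86 patients in each group". The authors then write "we assume a 20% drop-out rate", on the ground that these patients are less likely to finish, and conclude "The total sample size of 206 cases (per group was 103 cases) is required to reduce the underpower of the study". The Patients section confirms the allocation: "randomly allocated to an intervention or a sham-controlled group in a 1:1 ratio".

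Two other sections determine what a drop-out does to the analysis. Management and safety monitoring says that "information on patients with withdrawal will not be included in the final analysis". Data statistical analysis says the reverse: it invokes intention-to-treat, calls for everyone on the randomisation list to be in the final analysis, and provides for imputation of missing data.

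**The concern.** A drop-out rate is a fraction of those randomised. To retain a required number n after losing a fraction r, the number to randomise is n / (1 − r). Multiplying by (1 + r) gives too few, because the percentage is then taken of the completers. The printed 103 is what the second calculation gives.

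On the natural reading, the allowance exists to leave 86 patients with outcome data in each group, the number tied to 90% power. Under the protocol's own 20% assumption it does not. The three figures 86, 20% and 206 therefore do not fit together, and a results paper that repeats them would claim a protection the design does not have.

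**Working it through.** **Inputs** (protocol article, Sample size estimation): two-sided alpha 0.05; power 90%; 86 per group before drop-out; drop-out 20%; 103 per group and 206 in total; pilot means 5.97 and 4.79 with SDs 1.81 and 1.96. Allocation is 1:1.

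**1. Reproducing the printed total.**
- n × (1 + r) = 86 × 1.2 = 103.2, so 103 per group and 206 in total. This matches.
- n / (1 − r) = 86 / 0.8 = 107.5, so 108 per group and 216 in total (215 if 172 / 0.8 is rounded once on the total). This does not match.

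The first route is an inference from the match, since no inflation formula is printed.

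**2. What 206 leaves.**
- At 20% loss: 103 × 0.8 = 82.4, about 82 per group with complete data, 4 short of 86.
- Largest loss that still leaves 86: 1 − 86/103 = 0.165, or 16.5%.
- Shortfall in numbers randomised: 216 − 206 = 10 (9 with the single rounding).

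**3. Power if 86 per group gives exactly 90%.** The planning effect size is not stated, so it has to be backed out of the 86.
- Normal approximation: d = √(2/86) × (1.960 + 1.282) = 0.494.
- Power at 82 per group: Φ(0.494 × √(82/2) − 1.960) = Φ(3.165 − 1.960) = 88.6%.
- With the t-test, the d that gives exactly 90% at 86 is 0.497, and power at 82 is again 88.6%.

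The loss is about 1.4 percentage points.

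**4. Power on the printed pilot data.**
- Difference: 5.97 − 4.79 = 1.18.
- Pooled SD: √((1.81² + 1.96²)/2) = 1.886.
- d = 1.18 / 1.886 = 0.625.
- Power at 82 per group (t-test): 97.8%.
- Number needed for 90% power: 2 × (1.960 + 1.282)² / 0.625² ≈ 54 per group by the normal approximation, 55 by the t-test.

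So 86 does not follow from the printed pilot figures. Using either SD alone gives 50 to 58 per group, still well short of 86.

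**The case against.** The strongest reply has four parts.

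*Everyone is to be analysed.* If the intention-to-treat statement in Data statistical analysis governs, 103 per group enter the analysis and the drop-out step costs nobody. This stands in part. The protocol gives two incompatible rules, so it cannot be said without condition that drop-outs leave the analysis. But imputation does not restore the information in outcomes never observed, and if nobody were lost no inflation would have been needed.

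*The protocol never promises 86 completers.* True: it gives 86, then 20%, then 206, with no formula and no stated number of completers. That 206 was meant to preserve 86 is the natural reading of a drop-out allowance, but it is a reading.

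*The trial is not underpowered.* A reader might infer from the shortfall that it is. The documents do not support that. The loss is about 1.4 points on the assumption that 86 gives 90%, and on the only effect data printed, 82 per group has about 98% power. Nor may one treat a round standardised effect such as 0.50 as the design assumption; it is compatible with 86, but the protocol does not state it.

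*Drop-out may stay below 16.5%.* This is plausible, since the trial is a single session with its last assessment 5 minutes after the intervention. The 20% is nevertheless the protocol's own assumption, and the allowance has to be consistent with it.

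**Conclusion.** The statement is wrong as written, with low severity. Given 86 per group and 20% drop-out, the total should be 216 (108 per group). The printed 206 leaves about 82 per group with complete data and protects 86 only up to about 16.5% loss. The arithmetic is certain; that the authors multiplied by 1.2 is inferred from an exact match after rounding.

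The power figures are conditional: about 88.6% at 82 per group if 86 gives exactly 90%, and about 98% on the pilot means and SDs. The shortfall in analysed patients applies in full only if withdrawals are excluded. The gap between 86 and the roughly 55 implied by the pilot data is a separate and larger discrepancy. It does not make the drop-out step right, but it does mean the power consequence cannot be stated as one number until the derivation of 86 is known.

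**What to change.** Keep 206 and restate what it provides. Either wording would do:

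- 206 randomised leaves about 82 evaluable patients per group at 20% drop-out; or
- 206 randomised preserves 86 per group up to about 16.5% drop-out.

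In either case, show how 86 was obtained and recompute the power from the effect size and SD actually used for it. Do not write in an effect size chosen only because it reproduces 86. If the investigators prefer to keep both the 20% allowance and 86 completers, the consistent total is 216, which costs 10 more patients; the small loss of power does not by itself call for that.

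Reconcile the exclusion of withdrawals in Management and safety monitoring with the intention-to-treat statement in Data statistical analysis, so that the number analysed is unambiguous.

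The restatement costs one sentence plus the derivation of 86. It needs no change to recruitment or design; the stated power may come out about a point lower.
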